##### Changes in visceral and subcutaneous fat volume by MRI

Abdominal subcutaneous adipose tissue (abdominal SAT) and abdominal visceral adipose tissue (abdominal VAT) will be calculated from whole body axial T1-weighted fast spin echo scans (axial scans, 10 mm slice thickness followed by a 10-mm gap using the integral body coil). All images will be anonymised and blinded to time point, but not to subject (to facilitate matching anatomical landmarks), and analysed by Vardis (Vardis Group, London, UK) using SliceOMatic (Tomovision, Montreal, Canada), as described previously:^11^ the mean CoV for this methodology is total body fat, 1–2%; total subcutaneous fat, 3–4%; abdominal subcutaneous fat, 1–3%; visceral fat, 6–8%.

#### Monitoring/dispensing visits (6, 7, 10, 11)

These visits will involve a brief consultation with the study team to review glycaemic control (self-monitored capillary blood glucose), adverse effects and compliance (tablet count) and to collect supply of medication.

#### Pharmacovigilance

All adverse events will be reported and assignment of the severity/grading (mild, moderate, severe, life-threatening, death) made by the investigator responsible for the care of the participant. The assignment of causality will be made by the investigator. All non-serious adverse events (SAEs), whether expected or not, will be recorded and updated at each study visit. All new SAEs will be reported from the point of consent until 70 days after discontinuation of the investigational medical product (IMP); this includes those thought to be associated with protocol-specified procedures. Investigators will report SAEs, serious adverse reactions (SARs) and sudden unexpected adverse reactions (SUSARs) to LCTU within 24 hours of the local site becoming aware of the event. LCTU will notify the Medicines and Healthcare products Regulatory Agency (MHRA) and main REC of all SUSARs occurring during the study: fatal and life-threatening SUSARs within 7 days of notification and non-life-threatening SUSARs within 15 days. All adverse events will be followed until satisfactory resolution or until the investigator responsible for the care of the participant deems the event to be chronic or the patient to be stable.

#### Trial monitoring and oversight committees

The study will be overseen by the Trial Steering Committee (TSC). Day-to-day running of the trial will be coordinated by the Trial Management Group (TMG) supported by the LCTU, which will consist of the protocol committee members and the trial manager. The responsibilities will include
Report to the TSC.Maintain the Trial Master File.Confirm all approvals are in place before release of the trial treatment and the start of the trial at a site.Provide training about the trial.Provide study materials.Data management centre.Give collaborators regular information about the progress of the study.Respond to any questions (eg, from collaborators) about the trial.Ensure data security and quality and observe data protection laws.Safety reporting.Ensure trial is conducted in accordance with the ICH GCP.Statistical analysis.Publication of trial results.

The role of the TSC is to provide overall supervision of the trial. In particular, the TSC will concentrate on the progress of the trial, adherence to the protocol, patient safety and consideration of new information. The TSC must be in agreement with the final protocol and, throughout the trial, will take responsibility for:
Major decisions such as need to change the protocol for any reason.Monitoring and supervising the progress of the trial.Reviewing relevant information from other sources.Considering recommendations from the DMC.Informing and advising the TMG on all aspects of the trial.

The TSC will include experienced diabetes patients, other medical experts and clinical trialists. Meetings will be held at regular intervals determined by need, but no less than once a year. The ultimate decision for the continuation of the trial lies with the TSC.

### Outline of analysis

#### General approach

Continuous baseline characteristics will be summarised using mean, SD, median and interquartile range. Categorical variables will be summarised as frequencies and percentages. All point estimates will be considered to be statistically significant at the 5% level (two-sided) and will be presented with accompanying 95% CIs. No adjustment will be made for multiple comparisons.

#### Analysis

Primary and secondary outcome variables will be analysed using a covariance pattern linear mixed model (or other mixed model); the treatment effect will be adjusted for sex as a main effect (since it is a stratification factor), prerandomisation baseline values and the effect of period where relevant. An interaction test will be used to assess the treatment by period interaction (which may be indicative of a carry-over effect) and results interpreted cautiously if this is found to be significant at the 10% significance level. Although a common analysis strategy under such circumstances is to undertake a between-group treatment comparison using only the results from period 1, we follow the advice of Senn^19^
^20^ in avoiding doing so because of the inflation in the type I error rate when conducting such a comparison conditional on the interaction test being statistically significant.

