**Methods and analysis:**

This outpatient study will evaluate the effect of dapagliflozin (10 mg), compared with placebo, on food intake and energy expenditure at 7 days and 12 weeks. 52 patients with T2DM will be randomised to dapagliflozin or placebo for short-term and long-term trial interventions in a within participants, crossover design. The primary outcome is the difference in energy intake during a test meal between dapagliflozin and placebo. Intake data are collected automatically using a customised programme operating a universal eating monitor (UEM). Secondary outcomes include (1) measures of appetite regulation including rate of eating, satiety quotient, appetite ratings (between and within meals), changes in CNS responses to food images measured using BOLD-fMRI, (2) measures of energy expenditure and (3) changes in body composition including changes in liver fat and abdominal visceral adipose tissue (VAT) and subcutaneous adipose tissue (SAT).

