**Trial registration number:**

ISRCTN14818531. EUDRACT number 2013-004264-60.

Strengths and limitations of this studyThis is the first study to address the discrepancy between the estimated and actual weight loss as a result of SGLT2 inhibition in a prospective within participant study design incorporating short-term and long-term effects.The study is designed to assess macrostructure and microstructure of eating behaviour and the use of imaging modalities provide a neurophysiological and mechanical correlate.The sample size is relatively small, although provides sufficient power to answer the primary research question.The measurement of energy expenditure is performed using indirect calorimetry as opposed to the gold standard whole body calorimetry.There may be a carryover effect on body weight and body composition changes since there is no wash-out period between the long-term cross over, but any effect of this on the primary outcome (food intake) should be minimal.

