##### Liver fat by MRS and body fat volume by MRI (visit 0, 8, 12)

These measurements will be made at baseline, and at 14 and 26 weeks. Proton magnetic resonance spectroscopy of the liver will be performed as previously described.^11^ Three voxels of interest will be identified in the liver standard sites avoiding ducts and vasculature. In liver, voxel placement in post-treatment studies will be guided by reference to the pretreatment images. ^1^H MR spectra will be quantified using the AMARES algorithm in the software package jMRUI V.3.0. Intrahepatocellular lipid content (IHCL) is expressed as percentage of CH2 lipid signal amplitude relative to water signal amplitude after correcting for T1 and T2.^17^ Fat quantification by ^1^H-MRS has been validated against gold standard biochemical measurements.^18^ The mean interexamination coefficient of variation (CoV) for using this protocol is 7% (range 4–12%), and the mean intraexamination CoV is 6%.^17^

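### Carry-over is acknowledged for weight and body composition, but only the crossover estimate is planned for them and an unconditional week 14 comparison is not considered

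*Protocol article*

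**What the plan says.** The strengths and limitations list of the protocol article states: "There may be a carryover effect on body weight and body composition changes since there is no wash-out period between the long-term cross over". It limits the concern for the primary outcome only, saying that "any effect of this on the primary outcome (food intake) should be minimal".

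Liver fat, VAT and SAT are secondary outcomes (Abstract; Secondary objectives). Weight is measured (Table 2) and named in the carry-over statement, but it is not listed as a secondary outcome. For liver fat and body fat volume, "These measurements will be made at baseline, and at 14 and 26 weeks".

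The Analysis section applies one type of mixed model to primary and secondary outcomes alike. The treatment effect is adjusted for sex, "prerandomisation baseline values and the effect of period where relevant". A treatment-by-period interaction is tested, with "results interpreted cautiously if this is found to be significant at the 10% significance level". A between-group comparison restricted to period 1 after a significant test is declined "because of the inflation in the type I error rate when conducting such a comparison conditional on the interaction test being statistically significant". The section does not mention a period 1 comparison made regardless of that test.

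**The concern.** For the outcomes where the protocol itself sees a risk of carry-over, the only planned estimate is the one that carry-over biases. Adjusting for period does not remove the bias. Nor does adjusting for the pre-randomisation value, because that value is the same in both periods and cancels from the within-participant contrast. The interaction test may flag a problem, but it supplies no other estimate, and with this sample size it will often miss carry-over large enough to matter.

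One stated aim of the study is to quantify changes in fat distribution and liver fat. The size of the effect therefore matters, not only its significance. If part of the fat loss on dapagliflozin persists through the following 12 weeks on placebo, the reported effect will be too small, and nothing the plan commits to report would show by how much.

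**Working it through.** **Inputs from the protocol article.** N = 52, correlation 0.7, SD 165, difference 57.5 g, 80% power, two-sided 5%, 20% dropout (Sample size); placebo-subtracted weight loss 1.5–2 kg (Outcome measures).

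**Assumptions not in the article.** The carried-over fraction f; a correlation r of 0.7 to 0.95 for the fat outcomes (the article's 0.7 is for food intake), taken as equal between all occasions including baseline; effects of 0.3 to 0.8 SD; 41 completers, about 20.5 per long-term order.

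**1. The article's own figure.** SD of the difference = 165 × √(2 × (1 - 0.7)) = 127.8. A paired t-test for 57.5 needs n = 41 (power 0.803), and 41/0.8 = 51.25, so 52. The stated size is reproduced and is not in question.

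**2. Bias.** Let τ be the treatment effect and λ the carry-over into the second 12-week period. The between-group contrast has expectation τ at week 14 and τ - λ at week 26. The crossover estimate averages them: τ - λ/2. With λ = fτ this is τ(1 - f/2).

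| f (assumed) | Factor | 1.5–2.0 kg is estimated as |
|---|---|---|
| 0.25 | 0.875 | 1.31–1.75 kg |
| 0.5 | 0.75 | 1.13–1.50 kg |
| 0.75 | 0.625 | 0.94–1.25 kg |
| 1 | 0.5 | 0.75–1.00 kg |

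**3. The interaction test as safeguard** (r = 0.7, τ = 0.5 SD, f = 0.5, so λ = 0.25 SD; normal approximation).
- Unadjusted SE of the sequence-sum difference = √(2 × 2(1 + 0.7)/20.5) = 0.576 SD. Then 0.25/0.576 = 0.434, and power at the 10% level = Φ(0.434 - 1.645) + Φ(-0.434 - 1.645) ≈ 0.13.
- Adjusted for baseline, the variance of the sum is 2(1 - r)(1 + 2r) = 1.44, SE = √(2 × 1.44/20.5) = 0.375, and power ≈ 0.17.
- Crossover SE = √((1 - 0.7)/20.5) = 0.121 SD and bias = 0.125 SD. The nominal 95% interval therefore covers τ about 82% of the time.
- At r = 0.9, baseline-adjusted power is 0.29 and coverage 57%.
- Over effects of 0.3 to 0.8 SD, f from 0.25 to 1 and r of 0.7 or 0.9, baseline-adjusted power runs from 0.11 to 0.96. It is high only for large effects with near-complete carry-over.

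**4. Type I error** (simulation, 60,000 runs per setting, nominal 5%).

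| Rule | Type I error |
|---|---|
| Two-stage: 10% interaction test, then period 1 if significant | 0.082–0.094 (0.079–0.081 with baseline adjustment) |
| Period 1 test, given a significant interaction | 0.36–0.49 |
| Unconditional period 1 comparison | 0.050 |

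The article's reason is correct for the first two rows and does not apply to the third.

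**5. Precision.** Variance of the week 14 ANCOVA = 4(1 - r²)/n; of the crossover estimate = 2(1 - r)/n. The ratio is 2(1 + r), so the SE ratio is √3.4 = 1.84 at r = 0.7 and √3.9 = 1.97 at r = 0.95. For effects of 0.3 to 0.8 SD, week 14 power is 0.27 to 0.95 at r = 0.7 and 0.60 to 1.00 at r = 0.9.

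**The case against.** **The protocol made no error about period 1.** A reader might infer that it wrongly rejects period 1 analyses. It does not: it declines only the comparison made after a significant interaction test, and rightly so. This stands in full. The point is that the unconditional option is left unconsidered.

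**This is detail for the analysis plan, and the limitation is disclosed.** The section is an outline in a condensed article, and a fuller plan may exist. But it states one modelling approach for all outcomes and one response to suspected carry-over, and following them gives a biased estimate for outcomes the article itself flags. Disclosure does not bound the bias.

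**The interaction model already contains the week 14 contrast.** True for a two-period crossover, so it would be too strong to say that no valid estimate can be obtained from the plan. What is missing is a commitment to report it.

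**Carry-over is not established.** A reader might infer that the fat results will be understated. The article says only that carry-over may occur. It gives neither size nor direction, and a rebound after stopping (f below 0) would bias the estimate the other way. This stands.

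**The crossover estimate may still be the better one.** Its mean squared error is smaller until (fτ/2)² exceeds the variance saved. With n = 41 and τ = 0.5 SD, the saving at r = 0.7 is 4 × 0.51/41 - 2 × 0.3/41 = 0.0351, so f = √0.0351/0.25 ≈ 0.75. At r = 0.9 it is 4 × 0.19/41 - 2 × 0.1/41 = 0.0137, so f ≈ 0.47. This supports keeping the crossover estimate and setting the other beside it.

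**Preferring period 1 when the two differ brings back the conditional rule.** Correct: with complete, unadjusted data, the period 1 estimate minus the crossover estimate is half the interaction. No such rule should be written.

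**Conclusion.** The point holds in a limited form. For liver fat, VAT and SAT (and weight, if reported), the article acknowledges possible carry-over but plans only an estimate that is biased by half of it. Its safeguard has low power in most plausible settings and leads only to cautious wording. The bias is toward understatement if part of the dapagliflozin effect persists at week 26: 12.5% at f = 0.25, 25% at f = 0.5. The algebra is exact for the two-period comparison with complete data. The values of f, the correlations for fat outcomes, the effect sizes in SD units and the 41 completers are assumptions.

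The documents do not support saying that carry-over is expected, that the results will certainly be understated, or that the refusal of the conditional comparison is mistaken. The article also says the study is not formally powered for liver or visceral fat. The sample size and the primary food-intake analysis are not affected.

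**What to change.** For liver fat, VAT and SAT, and for weight if it is reported:

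- Pre-specify a between-group ANCOVA at week 14 on the pre-randomisation value, with sex in the model, as a supporting (sensitivity) analysis. Period 1 here means the first 12-week period. All participants take both 7-day treatments before it, and the article considers significant weight loss unlikely at that stage.
- Report it beside the crossover estimate every time, whatever the interaction test shows.
- State in advance which of the two is the main analysis, with no rule that chooses between them according to whether they differ or whether the interaction is significant.
- Leave the primary food-intake analysis as it is.

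The cost is one more model per outcome, on scans and weights already scheduled at baseline and around week 14. The week 14 interval will be about 1.8 to 2.0 times as wide as the crossover interval. It should be read as a check on the size of any bias rather than as a powered test.

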#### Rate of eating and satiety quotient

Cumulative intake data will initially be analysed for between-condition differences at each time point (every minute). These Dunnett's t-tests will be corrected conservatively for multiple comparisons (p<0.001). A standard technique for the examination of individual cumulative intake curves, relying on the visual judgement of deceleration by raters blinded to condition, will be used.^21^ This assessment will be quantified by raters calculating the coefficient of the start and end of individual cumulative intake curves to confirm their initial assessment. Curves whose coefficients are not lower at the end of the meal than at the start are classified as non-decelerating. The between-participant difference will be tested using a within participants χ^2^ test (McNemar test).

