## Methods and analysis

### Overall design, investigational plan and study population

This will be an outpatient, double-blind, placebo-controlled crossover study, to compare the effects of dapagliflozin with placebo on food intake and energy expenditure over periods of 7 days and 12 weeks. Fifty-two participants with T2DM will be recruited: aged 18–75 years, with glycated haemoglobin (HbA1c) <11% (97 mmol/mol) and either HbA1c ≥6.5% (48 mmol/mol) in patients who are not on sulphonylureas (eg, gliclazide, glimepiride), or HbA1c ≥7.0% (53 mmol/mol) in patients who are on sulphonylureas. Each participant will visit the study centre on 12 occasions: first, to undertake routine screening tests. If identified as eligible, subsequent visits involve consuming a test meal at baseline or following placebo or dapagliflozin 10 mg, respectively, and to undertake MR measurements. All patients will receive 7 days of dapagliflozin or placebo followed by 12 weeks of each treatment. Each participant will serve as their own control with the crossover between drug and placebo at short-term and long-term. The 7-day cross-over measurements will determine the short-term effects of energy loss on food intake and energy expenditure (at this stage, it is unlikely that significant weight loss would have occurred), while the long-term crossover at 12 weeks investigates the compensatory changes at dynamic stages of weight loss. The overall study design is illustrated (figure 1), with the full crossover design shown as study schematic (figure 2). Participants will be randomised to one of the four treatment sequences (figure 2).

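### Eating-rate curves: minute-by-minute Dunnett's t-tests at p<0.001 conflict with the protocol's own mixed model and no-adjustment rule, and do not suit a two-condition crossover

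*Protocol article*

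**What the plan says.** All places are in the protocol article.

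- **Rate of eating and satiety quotient**, first step: "Cumulative intake data will initially be analysed for between-condition differences at each time point (every minute"). The next sentence sets test and threshold: "These Dunnett's t-tests will be corrected conservatively for multiple comparisons (p<0.001"). Period, sex and baseline are not mentioned.
- **Same section**, deceleration: raters blinded to condition judge each curve, calculate coefficients at its start and end, and class it as decelerating or not. Then: "The between-participant difference will be tested using a within participants χ^2^ test (McNemar test").
- **General approach**: significance is at the two-sided 5% level, and "No adjustment will be made for multiple comparisons". No exception is stated.
- **Analysis**: "Primary and secondary outcome variables will be analysed using a covariance pattern linear mixed model", or another mixed model, adjusted for sex, baseline values and, where relevant, period.
- **Abstract, Methods and analysis**: "Secondary outcomes include (1) measures of appetite regulation including rate of eating, satiety quotient".
- **Overall design, investigational plan and study population**: "Each participant will serve as their own control with the crossover between drug and placebo at short-term and long-term".

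**The concern.** There are three separate problems.

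1. **Two multiplicity rules.** One section rules out any adjustment and works at 5%. Another adjusts and works at 0.001. Nothing says which governs the eating-rate result.
2. **Two analyses for one outcome.** Rate of eating is a secondary outcome and so falls under the mixed model, yet its own section describes t-tests at each minute. Two analyses on the books leave room to choose between them after the data are seen.
3. **A test that does not match the contrast.** Dunnett's procedure protects against comparing several groups with one control. Here the multiplicity comes from the minutes, not from several active arms, and the two conditions are measured in the same people.

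At stake is how clearly and how sensitively the trial can report a drug effect on the course of eating within a meal. The protocol offers this as the way to characterise how any increase in intake comes about.

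**Working it through.** **Step 1. Reproduce the protocol's own figure.** Inputs from Sample size: between-participant SD 165, correlation 0.7, difference 57.5 g (12.5% of 460 g), two-sided 5%, 80% power, paired t-test, 20% dropout.

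- SD of the within-participant difference = 165 × √(2 × (1 − 0.7)) = 127.8 g.
- The noncentral t distribution gives n = 41, with power 80.3%.
- 41 / 0.8 = 51.25, rounded up to 52. The stated 52 reproduces.

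**Step 2. What Dunnett's procedure does with one active condition.** Its critical value for one comparison with control, two groups of 41 (80 degrees of freedom), was simulated at 2.00. The ordinary t value is 1.99, so the two agree within simulation error. Naming Dunnett therefore corrects nothing, and it does not address the repeated minutes.

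**Step 3. What p<0.001 does.** It acts alone, as a Bonferroni-type limit. The family-wise error bound is the number of minutes × 0.001. Meal length is not given, so the range is assumed:

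| Minutes | Bound |
|---|---|
| 10 | 0.01 |
| 20 | 0.02 |
| 30 | 0.03 |
| 50 | 0.05 |
| 60 | 0.06 |

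The threshold is thus stricter than 5% overall for meals shorter than about 50 minutes. It is more conservative still because successive values of a cumulative curve are strongly correlated.

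**Step 4. What pairing is worth.** With 41 completers:

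- paired SE = 127.8 / √41 = 19.96 g;
- unpaired SE = 165 × √(2/41) = 36.4 g;
- ratio = 36.4 / 19.96 = 1.83, or 1/(1 − 0.7) = 3.3 on the variance scale.

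**Step 5. Illustrative power** for 57.5 g, 41 completers. The paired row is from the noncentral t. The second row is a simulation of an unpaired t-test applied to data that really are correlated at 0.7.

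| Error term | at 0.05 | at 0.001 |
|---|---|---|
| Paired | 80% | 27% |
| Pairing ignored | about 24% | about 0.2% |

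In the same simulation, the true type I error of the unpaired test at nominal 0.05 is about 0.0006.

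These inputs describe intake over the whole meal. The protocol gives no SD, correlation or target difference for any single minute, so the table shows the direction and rough scale of the loss and not the power of the minute-wise tests.

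**The case against.** **A specific section may override a general one.** The curve analysis can be read as an addition to the mixed model, and the objectives list rate of eating after the secondary objectives, as something further. This is a possible reading, but no exception is stated and the abstract calls the outcome secondary. The conflict stands.

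**The tests may be paired.** A reader might infer that the plan discards the crossover pairing. The text does not say so. It speaks of differences between conditions, uses a paired test a few lines later, and Dunnett contrasts can be formed with a within-participant error term. This objection stands: the unpaired row in the table is conditional. What remains is that the error term is not named.

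**Dunnett may have been meant for several meals against baseline.** There are five test meals, so this is possible, but the protocol does not say it.

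**A guard against repeated testing is sensible.** Agreed. The threshold is not too lenient, and strictness does not make it invalid. The objection is to a threshold that contradicts the general rule and is attached to a test chosen for a different multiplicity problem.

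**McNemar is a valid test.** Agreed. It suits a blinded yes/no classification of paired curves. Its reliance on discordant pairs is how it works, and preferring the continuous slope is a choice and not a correction. The phrase "The between-participant difference will be tested using a within participants" test is a slip of wording.

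**Conclusion.** The point holds as an inconsistency and a poorly matched method for a secondary outcome. It should be put right, but it does not threaten the trial. The primary outcome and the sample size of 52 are unaffected.

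As for size, the 0.001 threshold alone takes power from 80% to 27% in the illustration, even with pairing respected. Only if pairing were also ignored would it fall to about 0.2%. Both figures rest on whole-meal inputs and 41 completers.

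Two stronger readings are not supported:

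- A reader might infer that the eating-microstructure question would come out negative almost whatever the truth. That needs the unpaired reading, which is not stated. It also overlooks that the minute-wise step is only the initial one, and that the mixed model still covers secondary outcomes.
- A reader might put the unpaired power at 34% (at 0.05) and 4% (at 0.001). Those are powers for two independent samples and do not describe an unpaired test run on correlated crossover data.

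**What to change.** 1. Replace the minute-wise Dunnett tests with one within-participant mixed model of the cumulative curve: treatment, time in meal, treatment by time, period, sex, baseline and a participant-level covariance. Alternatively, summarise each curve by its coefficients and analyse those in the mixed model already specified. Test at 5% under the General approach and Analysis sections.
2. Keep minute-wise contrasts as description.
3. State in the eating-rate section that the general rules apply, so that one threshold and one model govern this outcome.
4. Keep McNemar for the blinded deceleration classification. Optionally, analyse the end-minus-start slope, which the raters already calculate, in the same mixed model.
5. In the McNemar sentence, describe the difference as between conditions and not between participants.

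The cost is a change of wording and slightly more modelling work. The data are the same and fewer tests are run.

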### Sample size

The primary outcome measure is energy intake after 12 weeks. On the basis of previous research,^12^ we estimate that 52 participants are required in order to detect a change in energy intake of 12.5% with 80% power and at a two-sided 5% level of significance. This estimate is based on a correlation between measurements of 0.7 and a between-participant SD of 165, both of which are based on a previous trial.^12^ The change in energy intake of 12.5% is based on a baseline consumption of 460 g in the test meal (ie, a 12.5% change equates to a change of 57.5 g). This calculation incorporates an allowance for participant dropout of 20%. The estimate was calculated using *PROC POWER* in SAS V.9.3 and is based on the paired *t*-test.

The study is not formally powered to detect differences in liver or visceral fat, but in a previous study we were able to detect a clear reduction or 7–11% of subcutaneous and visceral adipose tissue and a reduction in liver fat of 42% (IQR: −59.3 to −16.5%) with GLP-1 analogue treatment on a study of n=25 in a pre-post treatment analysis.^11^

Recruitment will take place over 12 months and will take place in Aintree University Hospital, Liverpool, UK (four to five patients per month). Participants will be recruited either from existing databases of volunteer patients, diabetes clinics in the hospital and community and by advertisement in the local press. The randomisation for each stratum will be performed within balanced blocks to ensure approximately equal numbers of participants across the treatment sequences within each stratum. The randomisation will be performed in two strata, female and male participants.

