##### Food intake and eating behaviour

Food intake and within meal assessment of hunger, fullness, desire to eat and prospective consumption will be collected using the Sussex Ingestion Pattern Monitor (SIPM V.2.0.13, University of Sussex), which comprises a concealed digital balance linked to a computer system. This system is similar to the UEM and allows continuous recording of food intake throughout a meal as well as custom programming for presentation of digital VASs pre-meal and post-meal, and at set intervals during the meal (every 150 g). Using this technology not only offers accurate collection of cumulative intake data, but also records data on subjective within meal measures of satiation. The assessment of within meal measures of satiation provides a behavioural correlate of satiety processes during a meal.^13^ Thus, the mechanisms by which potential increases in intake occur can be characterised; for example, intake may be increased due to weakened within meal satiation/delayed development of satiety. Eating rate during the meal can also be assessed using SIPM, as well as meal duration, satiety quotient and ratings of palatability, providing essential information about drug effects on the microstructure of eating. Pen and paper VAS measures of appetite (hunger, fullness, desire to eat, prospective consumption, satisfaction, thirst and nausea) fluctuations throughout the day will also be collected allowing analysis of drug effects on satiety between meals. Taken together these data fully characterise drug effects on appetite and eating behaviour. All intake, appetite and eating behaviour measurements are taken at baseline, 7 days, 14 days, 14 weeks and 26 weeks.

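### The minute-by-minute intake analysis names Dunnett's test at p<0.001 for a two-treatment within-participant contrast, and is not reconciled with the mixed model or the no-adjustment rule

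*Protocol article*

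**What the plan says.** Four parts of the protocol article bear on this.

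- **Rate of eating and satiety quotient** sets the minute-level analysis: "Cumulative intake data will initially be analysed for between-condition differences at each time point (every minute"), and then "These Dunnett's t-tests will be corrected conservatively for multiple comparisons (p<0.001"). Curve shape is classified next and compared with McNemar's test, which the article explicitly calls within-participant.
- **Analysis** sets the general model: "Primary and secondary outcome variables will be analysed using a covariance pattern linear mixed model (or other mixed model"). It is adjusted for sex, baseline and, where relevant, period. The abstract makes rate of eating one of the outcomes covered: "Secondary outcomes include (1) measures of appetite regulation including rate of eating, satiety quotient".
- **General approach** says that multiple comparisons will not be adjusted for.
- **Overall design** says: "Each participant will serve as their own control with the crossover between drug and placebo at short-term and long-term". Food intake and eating behaviour gives five meal occasions: "All intake, appetite and eating behaviour measurements are taken at baseline, 7 days, 14 days, 14 weeks and 26 weeks".

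**The concern.** The named test does not fit the contrast. Dunnett's procedure controls error when several treatments share one control, and its usual error term comes from independent groups. Each crossover has one active and one placebo condition. With two conditions there is nothing for Dunnett to adjust, and the standard form reduces to a two-sample t-test with no pairing and no period effect.

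Entering the five meal occasions as conditions does not help. The article names no control. Baseline as control would not compare dapagliflozin with placebo, and no single placebo occasion matches both the 7-day and the 12-week active occasions.

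Two internal conflicts add to this. Rate of eating falls under the mixed model as a secondary outcome, but the section that carries its name prescribes other tests and does not say which result counts. A correction to p<0.001 also contradicts the general statement that no adjustment is made.

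The stake is the account of how intake changes within the meal, which is why these data are collected. An insensitive test could leave a real difference unseen and be read as no change in the pattern of eating. The primary outcome is not affected.

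**Working it through.** **Inputs, all from Sample size.** Baseline intake 460 g; change 12.5%; between-participant SD 165; correlation 0.7; dropout 20%; paired t-test, two-sided 5%, 80% power. These describe total intake at the meal. The article gives no difference, SD or correlation for intake at a given minute.

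**Step 1. Reproduce the stated sample size** ("52 participants are required in order to detect a change in energy intake of 12.5% with 80% power and at a two-sided 5% level").

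- Difference: 0.125 × 460 = 57.5 g, as stated ("a 12.5% change equates to a change of 57.5 g").
- SD of a within-participant difference: 165 × √(2 × (1 − 0.7)) = 127.8 g.
- With the noncentral t, 41 completers give 80.3% power. 41 / 0.8 = 51.25, rounded up to 52. The stated figure is reproduced.

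**Step 2. Keep the pairing, change only the threshold.** With 41 completers the standard error is 127.8 / √41 = 19.96 g and the noncentrality is 57.5 / 19.96 = 2.88. The two-sided critical value rises from 2.02 at 5% to 3.55 at 0.001.

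| Paired test, 57.5 g | 41 completers | all 52 |
|---|---|---|
| two-sided 5% | 80% | 89% |
| two-sided 0.001 | 27% | 41% |

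At 0.001, 80% power would need 90 completers (113 randomised with 20% dropout), or a difference of about 88 g with 41 and 77 g with 52.

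**Step 3. Drop the pairing.** The unpaired standard error is 165 × √(2/41) = 36.4 g, which is 1 / √0.3 = 1.83 times the true 19.96 g. The observed difference must then exceed 1.99 × 36.4 = 72.5 g at 5%, or 3.42 × 36.4 = 124.5 g at 0.001. The paired limit at 0.001 is 3.55 × 19.96 = 70.9 g.

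- With the estimated standard error treated as fixed: (72.5 − 57.5) / 19.96 = 0.75, so about 23% power at 5%; (124.5 − 57.5) / 19.96 = 3.36, so about 0.04% at 0.001.
- Simulating correlated normal pairs (800,000 trials), which lets the standard error vary: 24% at 5% and 0.2% at 0.001. With all 52 it is 36% and 0.5%.

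The textbook two-sample formula gives 34% and 3.9% with 41. It assumes independent samples and so does not apply to paired data.

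**Step 4. Sensitivity to the correlation.** Paired power at 0.001 with 41 completers and the same SD and difference is 11% at correlation 0.5, 27% at 0.7, 50% at 0.8 and 91% at 0.9.

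**Step 5. What the threshold implies.** 0.05 / 0.001 = 50, so p<0.001 is Bonferroni for 50 tests. The number of minutes is not given. Cumulative intake at one minute contains intake at the minute before, so the tests should be strongly correlated, and a Bonferroni-type cut-off is stricter than family-wise 5% requires.

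**The case against.** A reader might infer that the plan definitely discards the pairing and has almost no chance of finding a difference in eating rate. The document does not support that.

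- **The error term is not stated.** A Dunnett comparison can use a repeated-measures error term, and the companion McNemar test is within-participant. The sub-1% figures belong to one reading only. With pairing kept, power is 27% to 41%.
- **No eating-rate effect is planned.** The 57.5 g is end-of-meal intake. At minute level the difference, SD and correlation will all differ, and step 4 shows how much the correlation alone matters.
- **The tests are a first step.** They can coexist with a mixed model of a summary rate, so a false finding of no change in eating rate need not follow.
- **This is a condensed article.** The choice of conditions, control and error term may be left to an analysis plan. The article openly calls p<0.001 conservative.

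These arguments limit the size of the problem but do not remove it. The article states a named test and a threshold, so this is not a matter of missing detail. The test is built for a different comparison, the threshold is costly even on the favourable reading, and both conflicts stand in the current text. The word initially does not say which analysis carries the conclusion.

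**Conclusion.** The point holds as a poorly chosen, unreconciled method for one supportive analysis, and it should be corrected. Dunnett's test is wrong for a two-treatment within-participant contrast. In standard form it ignores the correlation and period, and nothing in the text says otherwise. The section also conflicts with the general rule on multiplicity and leaves its relation to the mixed model open.

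As an illustration of size, moving from 5% to 0.001 cuts paired power at one time point from 80% to 27% with 41 completers, or from 89% to 41% with 52. If the test is run unpaired, power falls to about 24% at 5% and 0.2% at 0.001. All of this assumes that the end-of-meal difference, SD and correlation apply at the time point tested. It does not predict power for eating rate.

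**What to change.** In Rate of eating and satiety quotient:

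1. Replace the Dunnett tests by the within-participant comparison of dapagliflozin minus placebo, separately for the 7-day and the 12-week crossover, adjusted for period.
2. Name the mixed model from the Analysis section, fitted to a summary measure (mean eating rate or area under the cumulative intake curve), as the rate-of-eating result.
3. Label the minute-by-minute comparison supportive. Give it a family-wise 5% threshold that allows for correlation between minutes, for example a max-T permutation. The permutation must respect sequence and period; plain sign-flipping of differences would again ignore period.
4. Carry each participant's final intake forward after they stop eating, so that every minute includes everyone.
5. State in General approach that this is an exception to the rule of no multiplicity adjustment.

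The cost is a few sentences and a short extra program in place of a fixed cut-off. No new data or visits are needed.
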